## 2 STUDY OBJECTIVES AND ENDPOINTS

### 2.1 Objectives

#### 2.1.1 Primary

- To determine the recommended dose for expansion (RDE) or the maximum tolerated dose (MTD) for MP0317 as monotherapy in patients with advanced solid tumors (dose-escalation part only)
- To characterize the safety and tolerability of MP0317 as monotherapy in patients with advanced solid tumors

#### 2.1.2 Secondary

- To describe the PK of MP0317 as monotherapy in patients with advanced solid tumors
- To evaluate preliminary antitumor activity of MP0317 as monotherapy in patients with advanced solid tumors
- To evaluate preliminary clinical benefit of MP0317 as monotherapy in patients with advanced solid tumors

#### 2.1.3 Exploratory

- To evaluate pharmacodynamic effects of MP0317 as monotherapy in peripheral blood and tissue in patients with advanced solid tumors
- To evaluate the immunogenicity of MP0317 as monotherapy in patients with advanced solid tumors

### 2.2 Endpoints

#### 2.2.1 Primary

- Incidence of DLTs
- Type, incidence and severity of AEs and serious adverse events (SAEs) according to the National Cancer Institute Common Terminology Criteria for Adverse Events (NCI CTCAE) v5.0
- Changes between screening and post-screening laboratory parameters and vital signs

#### 2.2.2 Secondary

- Serum concentration-time profiles following first and repeated MP0317 infusions
- Determination of PK parameters including (but not limited to)  $C_{max}$ , time at  $C_{max}$  ( $T_{max}$ ), minimal serum concentration ( $C_{min}$ ), AUC, total clearance (CL), volume of distribution at steady state ( $V_{ss}$ ) and half-life ( $t_{1/2}$ )
- Overall response rate (ORR) based on best overall response (BOR) of complete response (CR) and partial response (PR) locally assessed using Response Evaluation Criteria in Solid Tumors (RECIST) v1.1 and immunotherapy RECIST (iRECIST)

CONFIDENTIAL

May not be used, divulged, published, or otherwise disclosed without the consent of  
Molecular Partners AG, Schlieren, Switzerland

- Disease control rate (DCR) of CR, PR or SD lasting 4 or more weeks following the initiation of MP0317
- Duration of response (DOR) of CR or PR based on RECIST v1.1 and iRECIST, time to progression (TTP) following the initiation of MP0317
- Progression-free survival (PFS) based on RECIST v1.1 and iRECIST
- Overall survival (OS)

### **2.2.3 Exploratory**

- Changes in frequency and functionality of B cells, DC, macrophages and T cell subsets in peripheral blood and tissue biopsies
- Assess FAP and CD40 expression and co-localization with MP0317 in tissue biopsies
- Changes in cytokines in serum
- Changes in sFAP and sCD40 in serum
- Circulating tumor DNA (ctDNA) (safety expansion part only)
- Occurrence of ADAs
- Incidence, titer and time-course of ADAs

## 3 STUDY DESIGN

### 3.1 Description of the Study

This is a phase 1, FIH, multicenter, open-label, dose-escalation study followed by a safety expansion part, evaluating the safety, tolerability, PK, pharmacodynamics and preliminary antitumor activity of MP0317 in adult patients with advanced solid tumors. See Sections 1.3.1 and 1.3.3 for the rationale behind the dose, regimen and DLT evaluation period.

The dose-escalation part is designed to determine the RDE or the MTD for MP0317 monotherapy. The safety expansion part is designed to confirm safety in a larger population (Figure 2). The dose-escalation scheme will use an adaptive study design following a Bayesian Logistic Regression Model (BLRM). A dose-escalation review committee (DERC) will monitor safety and govern all cohort dosing decisions (Sections 5.2.7 and 8.5).

The sponsor in consultation with the DERC may advise on the opening of cohorts with alternative dosing schedules (e.g. q1w). Such additional cohorts may be opened concurrently with the initial q3w dosing schedule cohorts, during dose escalation as well as during safety expansion phase.

Once the RDE (or MTD) has been determined for each schedule, the safety expansion cohorts will be opened and up to 15 additional patients in each cohort will be treated with MP0317 monotherapy at this dose.

The first doses between the first 2 patients in any cohort must be separated by a minimum of 7 days.

Study treatment will be administered as described in Sections 7.3.1 and 5.2.2.

Paired (pre and on-treatment) tumor and skin biopsies will be mandatory for all patients.

Biomarkers that may potentially correlate with antitumor activity or immunomodulatory effects of MP0317 may be explored during the study.

**Figure 2. Study Design**

[figure not shown]

Pts, patients; Q1W, every week dosing schedule; Q3W, every 3 weeks dosing schedule.

## 3.2 Number of Patients and Study Sites

A total of between 32 and 78 patients are anticipated, 17 to 30 during the dose-escalation part for the q3w schedule, 12 to 18 for the q1w schedule and 15 during the safety expansion parts for each schedule chosen for expansion.

The study will be conducted in France and the Netherlands, in 2 sites in each country. Additional sites and countries may be considered during the study.

## 3.3 Duration of Study

For individual patients, the screening period starts at the informed consent date, up to 28 days before the first study drug administration. Study treatment will be administered until the decision is taken for the patient to discontinue from treatment for any of the events described in Section 7.3.4 (i.e., end of treatment [EOT]).

A safety follow-up (FU) visit will be scheduled at Week 4 after the last study drug administration (Section 7.3.2). Completion of safety FU or discontinuation from the study for any reason defines patient end of study (EOS). Thereafter, survival FU will be performed to collect survival status approximately 3 and 6 months after patient EOS or until withdrawal of consent, patient is lost to follow-up, death or study termination by the Sponsor, whichever occurs first (Section 7.3.3).

The overall study duration is from the time of recruitment of the first patient until the overall EOS (Section 3.4). The duration of the study will depend on safety and efficacy events encountered during the dose-escalation and the safety expansion parts and the rate of patient accrual.

Estimated time from when the study opens to enrollment until completion of data analyses is Q3 2021 to Q3 2023.

## 3.4 End of Study

The overall EOS is defined as the date when the last patient/last visit occurs or when the last data point required for statistical analysis or safety FU is received from the last patient, whichever occurs later.

In addition, the Sponsor has the right to terminate or suspend the entire study or dosing schedules thereof, or close a given study site at any time for any reason (Sections 11.3 and 11.4). Such a decision will be communicated to the Investigators in writing.

## 3.5 Blinding and Randomization

This is an open-label, non-randomized study. Neither blinding nor randomization techniques will be used in this protocol. Patients, Investigators, site staff and persons performing the assessments and data analysts as well as the Sponsor will know the identity of the treatment throughout the study.

## 4 STUDY POPULATION

### 4.1 Patient Population

Patients who meet the inclusion and none of the exclusion criteria in Sections 4.2 and 4.3 will be eligible for participation in this study.

### 4.2 Patient Inclusion Criteria

A patient is eligible to be included in the study if they meet all of the following criteria:

1. Has an advanced, histologically-proven solid tumor of one of the following types, and for which approved therapies have been exhausted or for which the Investigator considers the patient ineligible or unable to tolerate other treatments:
  - a. Colorectal cancer
  - b. Ovarian cancer
  - c. Endometrial cancer
  - d. Gastric cancer
  - e. Pancreatic cancer
  - f. Anal cancer
  - g. Cervical cancer
  - h. Head and neck squamous cell carcinoma (HNSCC)
  - i. Mesothelioma
  - j. Prostate cancer
  - k. Non-small cell lung cancer (NSCLC)
  - l. Melanoma
  - m. Urothelial/bladder cancer
  - n. Microsatellite instability high cancer of any type
  - o. Cutaneous squamous cell cancer
  - p. Breast cancer
2.  $\geq 18$  years of age on the day of signing informed consent
3. Has signed and dated written informed consent before performing any study procedure, including screening
4. Eastern Cooperative Oncology Group (ECOG) performance status (PS) 0 to 1
5. Anticipated life expectancy  $\geq 12$  weeks by Investigator judgement
6. Measurable disease according to Response Evaluation Criteria in Solid Tumors (RECIST) v1.1
7. Should agree to undergo mandatory paired (pre and on-treatment) tumor biopsies and be considered to have biopsiable disease. The biopsies should be performed as follows:
  - a. At least 1 tumor lesion  $\geq 20$  mm amenable to percutaneous biopsy other than the target lesion(s) used to follow response as defined by RECIST v1.1.
  - b. For cutaneous or subcutaneous lesions, tumors should be  $\geq 5$  mm in diameter amenable to biopsy by excisional or punch biopsies without unacceptable risk of a major procedural complication.

- c. For core needle biopsy specimens, at least 3 to 6 cores with an 18-gauge needle should be collected.
- d. The on-treatment tumor biopsy should be taken from the same lesion as the pre-treatment biopsy. The biopsied lesion should be large enough to take both biopsies  $\geq 1$  cm apart.
- 8. Should agree to undergo mandatory paired (pre and on-treatment) skin biopsies
- 9. At least 28 days must have elapsed between any prior major surgery and screening. The following procedures are not considered major:
  - a. Obtaining the pre-treatment tumor and skin biopsies as per protocol requirements
  - b. Placement of a port for central venous access
  - c. Needle, punch or excisional biopsy of a clinically or radiographically detected lesion
- 10. Laboratory parameters at screening:
  - a. Hematology:
    - i. Platelet count  $\geq 100,000$  cells/mm^3
    - ii. Absolute neutrophil count  $\geq 1,000$  cells/mm^3
    - iii. Hemoglobin  $\geq 9$  g/dL
  - b. Serum creatinine  $< 1.5$  x upper limit of normal (ULN) or creatinine clearance  $> 50$  mL/min on the basis of Cockcroft-Gault glomerular filtration rate estimation
  - c. Coagulation:
    - i. International normalized ratio (INR)  $< 1.5$
    - ii. Prothrombin time (PT) and activated partial thromboplastin time (aPTT)  $\leq 1.5$  x ULN unless therapeutically warranted
  - d. Aspartate aminotransferase (AST) and alanine aminotransferase (ALT)  $< 3$  x ULN
  - e. Bilirubin normal, except for patients with known familial hyperbilirubinemia (such as Gilbert syndrome); for patients with documented Gilbert's syndrome (Gilbert-Meulengracht syndrome) total bilirubin  $\leq 3$  x ULN is acceptable
  - f. Albumin  $> 2.8$  g/dL or  $> 28$  g/L, and without albumin transfusion for  $\geq 7$  days before screening
- 11. Is using highly effective contraception, for females of childbearing potential (FCBP) and for men, as follows and as defined in Appendix 12.2:
  - a. Female: Is not pregnant, is not breastfeeding, and one of the following applies:
    - Not a FCBP
    - A FCBP who agrees and/or whose male partner agrees to follow the contraceptive guidance from screening, during the treatment period, and for at least 3 months after the last study drug administration. A FCBP must have a negative serum pregnancy test result at screening.
  - b. Male: Agreement to use a highly effective contraception method from screening, during the treatment period, and for at least 3 months after the last study drug administration and to refrain from donating sperm during this period.

### 4.3 Patient Exclusion Criteria

A patient will be ineligible if one or more of the following statements are applicable:

- 28. Known hypersensitivity to excipients used in the MP0317 formulation
- 29. Autoimmune diseases, except autoimmune endocrinopathies that are stable with hormone replacement therapy

30. Inflammatory diseases such as arthritis, colitis, liver fibrosis, cirrhosis, interstitial fibrosis or chronic obstructive pulmonary disease (COPD) that may have elevated tissue fibroblast activation protein (FAP) expression unless approved after consultation with the Sponsor
31. Serious illness or concomitant non-oncological disease considered by the Investigator to be incompatible with participating in the protocol
32. Left ventricular ejection fraction of  $< 50\%$  on echocardiographic exam or multi-gated acquisition (MUGA) scan at screening
33. History or evidence of clinically significant cardiovascular disease defined as at least one of the following criteria:
  - a. Evidence of poorly controlled arterial hypertension (systolic blood pressure  $> 160$  mmHg or diastolic blood pressure  $> 100$  mmHg)
  - b. Myocardial infarction or instable angina pectoris within 6 months before screening
  - c. Heart failure (New York Heart Association Class III or IV)
  - d. Any cardiac arrhythmia that is not well controlled
  - e. QT corrected (QTc) prolongation  $\geq$  Grade 2 ( $> 480$  ms) at screening measured on 2 separate electrocardiograms (ECG) at least 10 minutes apart
  - f. Clinically significant valvular heart disease
34. Severe dyspnea, pulmonary dysfunction or need for continuous supportive oxygen inhalation
35. Arterial thromboembolic event, stroke or transient ischemia attack within 12 months before screening
36. Known central CNS metastases that are either untreated or are treated but are associated with clinical symptoms (e.g. headache, convulsions); patients with CNS metastases that have been treated with radiotherapy and/or surgery are eligible if they are clinically without symptoms for at least 6 weeks before screening; if under treatment with corticosteroids (not exceeding 10 mg/day prednisone or equivalent) and/or anticonvulsive agents, patients must be on a stable dose for at least 14 days before first study drug administration.
37. Active uncontrolled bleeding or a bleeding diathesis
38. Therapy for active infection needs to be completed at least 7 days before first study drug administration
39. Known positivity for human immunodeficiency virus (HIV) or history of HIV (HIV testing is not mandatory)
40. Active hepatitis B (chronic or acute; HBV) defined as having a positive hepatitis B surface antigen (HBsAg) test at screening. Patients with past or resolved HBV infection (defined as having a negative HBsAg test and a positive hepatitis B core antigen antibody test) are eligible.
41. Active hepatitis C (HCV) infection defined as having a positive HCV antibody test followed by a positive HCV ribonucleic acid (RNA) test at screening. The HCV RNA test will be performed only for patients who have a positive HCV antibody test. Patients who are positive for HCV antibodies are eligible only if polymerase chain reaction (PCR) is negative for HCV RNA.
42. Serious or non-healing wound, skin ulcer or non-healing bone fracture
43. Abdominal fistula, gastrointestinal perforation or intra-abdominal abscess within 6 months before screening
44. Any vaccine within 28 days before first study drug administration (clarification in Section 6.5)
45. An allogenic tissue/solid organ transplant
46. History of another primary malignancy except for:

- a. Malignancy treated with curative intent and with no known active disease  $\geq 2$  years before screening and of relatively low potential risk for recurrence
  - b. Adequately treated non-melanoma skin cancer or lentigo maligna without evidence of residual disease
  - c. Adequately treated carcinoma in situ without evidence of disease
  - d. Cancer patients with incidental histologic findings of prostate cancer that, in the opinion of the Investigator, is not deemed to require active therapy (e.g. incidental prostate cancer identified following cystoprostatectomy that is tumor/node/metastasis Stage  $\leq$  pT2N0) may be eligible, pending discussion and approval by the Sponsor
- 47. Previous treatment with a DARPin® molecule
  - 48. Concurrent enrollment in another clinical study, unless it is an observational (non-interventional) clinical study or it is the follow-up period of an interventional study
  - 49. Use of an investigational agent within 28 days before first study drug administration
  - 50. Any anticancer treatment, including chemotherapy, hormonal therapy or radiotherapy, within 21 days before first study drug administration; however, the following are allowed:
    - a. Hormonal therapy with gonadotropin-releasing hormone (GnRH) agonists or antagonists
    - b. Hormone-replacement therapy or oral contraceptives
    - c. Palliative radiotherapy for bone metastases within 14 days before first study drug administration
  - 51. Continuous corticosteroid use exceeding 10 mg/day prednisone or equivalent
  - 52. Any condition that, in the opinion of the Investigator, would interfere with evaluation of the investigational medicinal product (IMP) or interpretation of the patient's data
  - 53. Unable or unwilling to comply with all study requirements for clinical visits, examinations, tests and procedures
  - 54. Patient deprived of liberty by a judicial or administrative decision, patient admitted to a social institution or who is under a measure of legal protection, patient hospitalized without consent or who is in an emergency situation

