### 5.2.5 Dose-Limiting Toxicities

DLT evaluation and a recommendation regarding dose-escalation steps will be made by the DERC (Section 8.5), after consideration of all available safety information.

A DLT is defined as an AE or abnormal laboratory result meeting any of the criteria below, that is assessed by the Investigator as related to study treatment, and that occurs within the DLT evaluation period, including death (Section 5.2.6). Severity of all AEs will be assessed according to NCI CTCAE v5.0.

- Any  $\geq$  Grade 3 study drug-related non-hematologic AE, including the following abnormal laboratory results: Hepatic laboratory parameters potentially fulfilling Hy's Law criteria: AST or ALT  $\geq 3 \times$  ULN and concomitant total bilirubin  $\geq 2 \times$  ULN
- Any Grade 4 study drug-related hematologic AE or abnormal laboratory result (hematologic or non-hematologic)
- Grade 3 neutropenia lasting  $> 7$  days despite adequate standard-of-care medication
- Grade 3 or 4 febrile neutropenia (fever  $\geq 38.5$  °C)
- Grade 3 anemia that cannot be adequately treated by blood transfusions
- Inability to administer the next dose due to a drug-related AE or delayed administration of the next dose due to a drug-related AE and/or abnormal laboratory result lasting  $> 14$  days despite adequate medication
- Any other AE/abnormal laboratory result which, in the view of the Investigator and/or Sponsor, is deemed clinically significant and considered a DLT

Note that the following AEs/abnormal laboratory results, some of which are expected with the study treatment, will not be considered a DLT:

- Any transient Grade 3 or 4 abnormal laboratory results without any related clinical symptoms and lasting  $< 72$  h
- Grade 3 events that have not been optimally treated with standard-of-care medication, lasting  $< 7$  days
- Grade 4 amylase or lipase not associated with symptoms or clinical manifestations or radiologic signs of pancreatitis

- Grade  $\geq 3$  lymphocytopenia not associated with symptoms or clinical manifestations
- Grade 3 hypertension resolving within 48 h
- Grade 3 IRR resolving under adequate treatment (first event only)
- Grade 3 fatigue lasting  $\leq 14$  days

An AE considered by the Investigator to be disease-related should not be considered a DLT.

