## 5.2.6 Dose-Limiting Toxicity Evaluability

The evaluability rules for DLT assessment apply to dose-escalation cohorts only.

The DLT evaluation period is defined as the 4-week period after first study drug administration.

Patients evaluable for DLT must either a) receive at least 2 administrations of MP0317 at q3w dosing schedule or 3 administrations at q1w dosing schedule at the assigned dose level and be observed until pre-dose of Cycle 2 Day 8 or b) experience a DLT as defined in Section 5.2.5 during the DLT evaluation period.

A patient will not be considered as DLT evaluable and may be replaced if they experience any of the following events during the DLT evaluation period:

- Received an MP0317 dose which is less than 90% or more than 110% of the planned infusion dose.
- Discontinued from treatment due to AE or death unrelated to study treatment, withdrawal of consent, lost to follow-up or Investigator decision (unrelated to study treatment).

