## **6.4 Anticancer Treatment**

Concomitant use of anticancer treatment other than MP0317 is specified in Section 4.3.

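### The bone-radiotherapy exception does not fit the 21-day rule it modifies: as written, irradiation 1 to 14 days before first dose is accepted and irradiation 15 to 21 days before is refused

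*Protocol*

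**What the plan says.** The stem of criterion 50 in Protocol Section 4.3 excludes "Any anticancer treatment, including chemotherapy, hormonal therapy or radiotherapy, within 21 days before first study drug administration; however, the following are allowed". Item c of the list that follows reads "Palliative radiotherapy for bone metastases within 14 days before first study drug administration". Criteria 23 and 23c of the Protocol Summary carry the same rule in the same words.

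Section 6.4, where a reader would look for further guidance, says only that "Concomitant use of anticancer treatment other than MP0317 is specified in Section 4.3". Section 7.2.1 rules out waivers and directs eligibility questions to the sponsor.

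On the consequences, Section 5.2.6 states that "The DLT evaluation period is defined as the 4-week period after first study drug administration". Section 5.2.5 limits DLTs to an event "that is assessed by the Investigator as related to study treatment, and that occurs within the DLT evaluation period" that also meets one of the listed criteria.

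**The concern.** A washout normally becomes easier to satisfy as the interval lengthens. This one does not: the shortest intervals pass, the middle ones fail and the long ones pass again.

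The likely mechanism is visible in the drafting. Criteria 44 and 49 and the stem of criterion 50 all use the within-so-many-days form to mark a period that is forbidden. In 50c the same form sits in a list of what is allowed, so it marks a period that is permitted. Where the list wants a minimum gap it uses different words, as in criterion 38: "Therapy for active infection needs to be completed at least 7 days before first study drug administration".

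Two things are at stake. First, sites may apply the criterion differently, and a site that quietly corrects it departs from a protocol that grants no waivers. Second, acute effects of irradiation given shortly before first dose could overlap the DLT window and the Cycle 1 biomarker sampling. Cohorts have 1 to 3 or 3 to 6 patients (Table 3), so one event that is hard to attribute carries weight.

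**Working it through.** The protocol gives no figure to reproduce. The check is a day count.

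**Inputs**
- Exclusion: radiotherapy 1 to 21 days before first dose (criterion 50, synopsis 23).
- Exception: palliative bone radiotherapy 1 to 14 days before first dose is allowed (50c, synopsis 23c).
- Convention assumed: the day before first dose is Day -1, and both limits are inclusive. If both were exclusive, the closed band would move by one day and still be seven days long.

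**Rule as written.** With d the number of days before first dose, a patient passes if d > 21 or d ≤ 14. The patient fails if 15 ≤ d ≤ 21, which is 21 - 14 = 7 days.

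**Comparison with two coherent alternatives.** These only show how far readings can diverge; neither is recommended.

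| Reading of 50c | Accepted | Refused |
|---|---|---|
| As written | Days -14 to -1; Day -22 and earlier | Days -21 to -15 (7 days) |
| 14 days as a minimum gap | Day -14 and earlier | Days -13 to -1 (13 days) |
| Bone radiotherapy exempt throughout | All days | None |

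The first two readings give opposite answers on Days -13 to -1 and on Days -21 to -15, that is 13 + 7 = 20 of the 21 days, and agree only on Day -14. The first and third differ on the 7 days from Day -21 to Day -15.

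**Does either intent rescue the text?** If a shorter washout was meant for palliative bone treatment, the words state the reverse. If recent palliative treatment was meant to be allowed, nothing explains why Days -21 to -15 stay closed. Both intents leave a conflict between stem and exception.

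**Does another section settle it?** The synopsis repeats the wording, Section 6.4 points back to Section 4.3, and Section 7.2.1 supplies no alternative rule.

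**The case against.** The strongest reply is that the practical harm is small, and much of that stands.

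- The irradiation itself precedes the DLT window, which opens at first dose. Only its after-effects can fall inside.
- A DLT must be judged related to study treatment. Section 8.1.1 requires positive grounds for relatedness and consideration of alternative causes, including concomitant treatment.
- Section 5.2.5 removes several plausible radiotherapy effects from the DLT definition: Grade 3 fatigue of up to 14 days, lymphocytopenia without symptoms, and transient laboratory changes without symptoms.
- Criterion 10 sets blood-count limits at entry. Under Section 7.4.11, values from the 48 hours before dosing inform suitability.
- Criterion 52 excludes conditions that would interfere with evaluation, and under Section 7.2.2 the sponsor's medical monitor reviews each eligibility form.

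A reader might also infer that the flaw can be sized from Table 30. With no DLTs at lower doses, moving from 0/3 to 1/3 DLTs at 1 mg/kg raises the overdose probability at 3 mg/kg from 0.055 to 0.306, past the 25% limit of Section 9.4.1.1. The documents do not support that use. Any single DLT has this effect, whatever its cause. The protocol offers no probability that a patient has such radiotherapy, develops a qualifying toxicity and has it misattributed. The shift is also recoverable: after a further 0/3 at 1 mg/kg, Table 30 gives 0.18.

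Nor is confounding of the biomarker readouts shown. Skin samples come from normal skin (Section 7.4.16.2), and nothing says the biopsied tumor lesion is an irradiated one (Section 7.4.16.1). Sections 1.1 and 1.3.2 name radiotherapy as a future combination partner, which makes an influence conceivable but does not establish it.

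These points limit the consequence. They do not make the criterion coherent, and case-by-case judgement does not replace a rule that sites can follow as written.

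**Conclusion.** The point holds as an eligibility rule that gives an incoherent result when followed exactly. For palliative bone radiotherapy, seven days (Days -21 to -15) are refused while the fourteen days closer to dosing are accepted, identically in Section 4.3 and the synopsis. This rests only on the plain meaning of the two clauses and the day convention stated above.

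The consequence for the trial is a possibility, not a demonstrated bias: harder attribution of early events in small cohorts and possible overlap with early biomarker sampling, both limited by the safeguards listed.

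A reader might conclude that the sponsor must have meant a minimum gap. The documents do not establish that intent. Permitting such treatment throughout the 21 days would remove the inconsistency equally well.

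**What to change.** Reconcile the 21-day stem with the 14-day exception in Section 4.3 (50 and 50c) and in the synopsis (23 and 23c). The result should be one coherent rule across the whole 21-day period, in identical words in both places, so that all sites apply it the same way. The interval or permission is the sponsor's clinical decision and is not proposed here.

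The cost is a short wording change in two places at the next amendment. Depending on the rule chosen, some patients may have their first dose deferred, or some now excluded may become eligible. No change to the dose-escalation model or sample size is needed.
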